## Abstract

**Background:**

Accidental injury represents the most common type of traumatic event to which a child or adolescent may be exposed, with a significant number of these children going on to experience posttraumatic stress disorder (PTSD). However, very little research has examined potential interventions for the treatment of PTSD in these children. The present trial aims to evaluate and compare child- and family-focused versions of a cognitive-behavioural early intervention for PTSD following accidental injury.

**Methods/Design:**

The principal clinical question under investigation is the efficacy of an early, trauma-focused cognitive-behavioural intervention for the treatment of PTSD in children following accidental injury. Specifically, we compare the efficacy of two active treatments (child-focused and family-focused CBT) and a waitlist control (no therapy) to determine which is associated with greater reductions in psychological and health-related outcome measures over time. The primary outcome will be a reduction in trauma symptoms on a diagnostic interview in the active treatments compared to the waitlist control and greater reductions in the family-compared to the child-focused condition. In doing so, this project will also trial a method of stepped screening and assessment to determine those children requiring early intervention for PTSD following accidental injury.

**Discussion:**

The present trial will be one of the first controlled trials to examine a trauma-focused CBT, early intervention for children experiencing PTSD following accidental injury (as opposed to other types of traumatic events) and the first within a stepped care approach. In addition, it will provide the first evidence comparing the efficacy of child and family-focused interventions for this target group. Given the significant number of children and adolescents exposed to accidental injury, the successful implementation of this protocol has considerable implications. If efficacious, this early intervention will assist in reducing symptoms of traumatic stress as well as preventing chronic disorder and disability in children experiencing acute PTSD following accidental injury.

**Trial Registration:**

Controlled-trials.com: ISRCTN79049138

## Background

Posttraumatic Stress Disorder (PTSD) is an anxiety disorder that can develop following exposure to various traumatic events. It consists of three core symptom clusters; re-experiencing of a traumatic event, emotional numbing or avoidance of reminders of that event and physiological hyperarousal. Children and adolescents may experience PTSD following exposure to a wide variety of traumatic events, including sexual or physical abuse, war, natural disasters, accidents and medical-related traumas. The trauma that triggers the development of PTSD may be either of a recurring nature (e.g., ongoing sexual or physical abuse), or it may be a single incident trauma (e.g., exposure to natural disaster, motor vehicle accident (MVA) or injury).

Approximately 25% of children and adolescents report experiencing a significant traumatic event by the age of 16 years [1]. In Australia, accidental injuries (e.g. bicycle accidents, burns, sporting injuries) represent the most common type of traumatic event experienced by youth, with approximately 2,500 per 100,000 (2.5%) children and adolescents experiencing a serious accidental injury necessitating a hospital admission each year [2]. Although the majority of youth demonstrate great resilience or appear to be only briefly affected by such traumatic events, a significant minority of young people will develop PTSD or other psychological difficulties following exposure to a traumatic event or ongoing trauma. A recent meta-analysis reported average prevalence rates ranging from 0% to 37.5% for children who have experienced any kind of accidental injury (including MVAs, but also other accidental injuries such as burns and sporting injuries), with an average prevalence of 19.82% [3]. Prevalence rates appear to differ according to factors such as the type of injury sustained and in particular, the method of measurement used (e.g. self-report versus diagnostic interview and the use of full or partial diagnostic criteria). For instance, Aaron, Zaglul and Emery [4] reported that 22.5% of participants met criteria for PTSD following a physical injury, although this increased to 47.5% when considering partial PTSD.

Importantly, recent research has indicated little difference in terms of distress and impairment between children meeting full and partial criteria for PTSD [5]. Several alternative approaches have been proposed for the classification of PTSD in youth, which take into account developmental differences in youth experiencing posttraumatic stress. Specifically, Scheeringa and colleagues [6,7] have proposed an alternative PTSD algorithm ("PTSD-AA algorithm"), which removes Criterion A2 (initial response of fear, helplessness or horror) and requires only one re-experiencing symptom, one symptom of avoidance (as opposed to three) and two of hyperarousal. The PTSD-AA algorithm has now been tested in several studies and has been demonstrated to be a better predictor than DSM-IV criteria of psychosocial functioning [7,8]. This suggests that the number of children suffering emotional problems after a traumatic event may be much higher than the prevalence percentages suggested by studies requiring that full diagnostic criteria be met. It also highlights the importance of studying children and adolescents who meet criteria for not only the full PTSD diagnosis, but also the alternative algorithm (PTSD-AA). From this point onwards, the term PTSD will be used to refer to young people experiencing either full PTSD or meeting the PTSD-AA algorithm.

In terms of consequences, PTSD is a chronic and debilitating disorder that is associated with significant impairments in both social and academic functioning [9]. When considering children who have experienced accidental injury specifically, PTSD is also associated with elevated rates of other emotional and behavioural problems (especially anxiety disorders), in comparison to community samples and children admitted to hospital for non-trauma related health reasons [10]. Further, PTSD is also associated with poorer health-related quality of life for children (i.e., the impact of disease and therapy on a person's life situation), both in the short-term and the long-term, including poorer adherence to medical protocols [11].

### Interventions for childhood PTSD

Trauma-focused CBT (TF-CBT) has demonstrated the strongest level of empirical support as the treatment of choice for PTSD in adults. Specifically, models of the psychological impact of trauma suggest that the way in which people remember and recount threatening events significantly affects how well they manage and adjust to those experiences [12]. Similar models of TF-CBT have also been described for childhood PTSD [13]. In the child and adolescent literature, the evidence base is also strongest for TF-CBT interventions [14-16], however the vast majority of research has examined a very narrow sub-group of traumatic events that may affect children and adolescents (e.g. sexual abuse). Unfortunately, accidental injuries represent a sub-group of traumatic events affecting children and adolescents that is far more commonly encountered and yet has received only very little scientific attention. It is possible that this group of sufferers may present with different symptoms to those experiencing ongoing sexual abuse or repetitive trauma and subsequently, may require different treatment approaches [17].

In light of these important differences, it has been suggested that the generalization or application of knowledge gained from treatment outcome studies with young people who have experienced child sexual abuse to young people who have experienced trauma other than abuse may be highly problematic [18]. In more recent years, Cohen and colleagues' TF-CBT has demonstrated efficacy for children who experience PTSD following traumatic events other than sexual abuse, including traumatic grief, domestic violence, terrorism, natural disasters and multiple traumatic events [15]. However, a review of the literature indicates only a handful of controlled trials that have been published examining TF-CBT for children with PTSD following a single-incident trauma.

Chemtob, Nakashima and Hamada [19] and Stein and colleagues [20] provided school-based interventions to children experiencing trauma symptoms following a hurricane and exposure to violence respectively. Both studies concluded that the child-focused interventions evaluated resulted in significant reductions in self-reported PTSD scores. Although extremely important, neither of these studies included a WL condition, nor did they utilise diagnostic status as a primary outcome measure. In a more recent controlled trial, Smith and colleagues [21] compared an individual child-focused CBT condition (in which joint parent-child sessions were carried out as deemed appropriate) to a WL condition, in a sample of 24 young people who met full criteria for PTSD following either an MVA or exposure to violence. They reported that individual TF-CBT was effective in reducing indicators of PTSD in children and adolescents who had experienced a single incident trauma. However, the number of participants was extremely small and the intervention evaluated does not appear to have been uniformly administered to all participants (this is particularly relevant when considering to what extent parents were involved in treatment). Importantly, none of the studies to date appear to have examined health-related outcomes such as physical functioning or adherence to medical protocols.

Overall, research has demonstrated strong support for TF-CBT in the treatment of childhood PTSD, however, controlled investigations of youth exposed to single-incident traumas are lacking. On the limited evidence available, it appears that trauma-focused CBT may be an effective treatment for PTSD in children and adolescents exposed to accidental injuries such as MVAs. However, more controlled trials and empirical evidence is required and several important questions remain unanswered, including the importance of parental involvement in treatment and optimal timing of interventions.

### The role of parents in the treatment of PTSD in children and adolescents

The role of parenting behaviours and parental anxiety have long been recognised as crucial factors in the development and maintenance of childhood anxiety disorders [e.g. [22]]. Recent research also supports the proposal that family-focused CBT results in significantly better long-term outcomes for children with anxiety disorders. For example, Cobham, Dadds, Spence, & McDermott [23] reported that, 3 years after completion of treatment, anxiety-disordered children/adolescents who had received family-focused CBT were significantly more likely to be anxiety diagnosis-free (92%) compared with those who had received child-focused CBT (69%). Increasingly, it is being acknowledged that parental reactions, psychopathology and coping strategies all have the potential to play an important role in the development and maintenance of children's PTSD [e.g. [24,25]].

To date, very few treatment studies in this area have included a parental treatment component, with those that have concluding that a combined parent and child trauma-focused CBT condition results in the best outcomes for children. Although the recent pilot study conducted by Smith et al. [21] did include some degree of parental involvement, this was not quantified and did not appear to be administered in a standardized fashion across participants. From the limited evidence available it is clear that an important direction for future research centres around the question of whether involving parents in treatment significantly enhances child-focused CBT for PTSD.

### The importance of early intervention

Another issue which requires attention concerns the optimal timing for delivery of CBT interventions for childhood PTSD. In terms of the course of PTSD in children and adolescents, the current adult literature and the few existing prospective studies of children presenting with PTSD suggest that a steep decline in PTSD rates may be expected within the first year following the traumatic event [26-28]. However, a significant proportion of children who initially present with PTSD following a traumatic event are highly likely to continue to experience PTSD over the long-term if they do not receive treatment. There is then a fine balance to be struck between the need to provide early intervention in order to prevent the development of emotional and behavioural problems after trauma, and the need to avoid treating young people who do not need treatment and would instead recover on their own.

Strategies for identifying those most at risk for the development or continuation of poor psychological adjustment after trauma may represent the best way forward. Kenardy and colleagues [10] reported that early self-reported symptoms of PTSD in children injured in accidents (measured at 1-2 weeks post-injury) predicted the presence of PTSD symptoms at 4-6 weeks and 6 months post-injury. Using a specially developed scale (the Child Trauma Screening Questionnaire; CTSQ), the diagnosis of 91% of children was correctly predicted in this study. Thus, it is possible to identify those children most likely to be 'at-risk' of PTSD diagnosis within the first two weeks following the injury. Moreover, it is proposed that early intervention targeted at children who demonstrate the presence of PTSD symptoms at 4-6 weeks, will be effective in significantly reducing the longer-term prevalence of PTSD and anxiety disorder symptoms.

Thus, there is a pressing need for a controlled trial examining the efficacy of a trauma focused, CBT early intervention for the treatment of PTSD in children following exposure to accidental injury. Further, a controlled trial examining the impact of CBT on psychosocial as well as health related outcomes is necessary. A trial of this sort provides the opportunity to examine whether trauma-focused CBT interventions are suitable for PTSD resulting from accidental injury, as opposed to repetitive trauma such as sexual abuse or natural disasters. Given the importance of parental involvement in the treatment of other child anxiety disorders, yet the lack of examination of this issue in the treatment of youth PTSD (overall), there is also a need to examine whether CBT interventions can be enhanced through the addition of a parent-based component.

The study protocol presented here provides an overview of the present trial including a description of the methods, design, and current status of the trial as well as a discussion of the possible implications that may arise from the findings.

## Methods/Design

### Design of the Trial

This study is designed as a three arm randomised controlled trial with two active interventions ('*child-focused' *and *'family-focused'*) and one comparison (*'waitlist'*) condition. The study will be conducted across 3 hospitals in Australia, The Royal Children's Hospital (RCH) in Brisbane, The Mater Children's Hospital (MCH) in Brisbane and the Women's and Children's Royal Hospital (WCH) Adelaide. There will be six measurement occasions: screening at 1-2 weeks post-hospital admission, baseline, 4-weeks post-baseline, post-intervention, and follow-ups at 6 and 12 months after the post-intervention assessment. A half crossover design will be used to allow baseline and post-test comparisons between the two active treatment conditions and waitlist control group on primary and secondary outcome measures, as well as increasing the sample size for the final evaluation at follow-up. Thus, all children in the waitlist condition will be randomly allocated to one of the two active treatment conditions following their initial waiting period.

This study was granted ethical approval by the University of Queensland Human Research Ethics Committee (protocol number2008002119), the Royal Children's Hospital (Brisbane) Children's Health Service District Ethics Committee (protocol number HREC/09/QRCH/41), The Mater Health Services (Brisbane) Human Research Ethics Committee (protocol number 1305C) and the Children Youth and Women's Health Services (Adelaide) Human Research Ethics Committee (protocol number REC2149/2/2112). The study is funded by an NHMRC Project Grant (569660). The measures to be administered at each time point are listed in Table 1.

**Table 1 T1:** Measures to be administered at each measurement occasion

Measure	Screening	Baseline	4-weeks post-baseline	Post-test	6-month	12-month
Demographics	X	X				
Child Trauma Screening Questionnaire	X	X	X	X	X	X
Heart-rate	X					
Injury severity	X					
Clinician Administered PTSD Scale-Child and Adolescent Version		X	X	X	X	X
Faces Pain Scale		X		X	X	X
Child PTSD Symptom Scale		X	X	X	X	X
Child Depression Inventory-Revised		X		X	X	X
Spence Children's Anxiety Scale		X		X	X	X
Pediatric Quality of Life Scale - Child version		X		X	X	X
Child Behavior Checklist		X		X	X	X
State Trait Anxiety Inventory		X		X	X	X
Pediatric Quality of Life Scale - Parent version		X		X	X	X
Depression, Anxiety and Stress Scale		X		X	X	X
Posttraumatic stress Diagnostic Scale		X	X	X	X	X
Satisfaction/Credibility Questionnaire				X		
Global Functioning/Improvement Scale			X	X	X	X

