#### Stage 4 - Intervention

Participants who fulfill either full or partial diagnostic criteria for PTSD and agree to participate in the study will be randomly assigned to either the waitlist condition (WLC) or one of the two active treatment conditions; child-focused cognitive-behavioural therapy (CF-CBT) or family-focused cognitive-behavioural therapy (FF-CBT). Participants in the WLC will be randomly assigned to one of the two active treatment conditions after 10 weeks of having been in the WLC (following a re-assessment at this time).

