#### Stage 6 - Post-intervention assessment and follow-up

All participants will be followed up at post-intervention and 6 and 12 months following the completion of treatment, using the assessment battery outlined in Table 1 and described below. In addition, as noted earlier, families in the waitlist condition will be re-assessed following completion of the 10-week monitoring period. The Research Assistants involved in conducting pre-treatment and follow-up assessments will be blind to participants' treatment condition.

This study will aim to recruit a total of 140 participants (approximately 45 in each condition). Recruitment will be carried out over an 18-24 month period at three hospital sites. A comparison of the two active treatments to the waitlist control condition will establish the basic efficacy of both CF-CBT and FF-CBT. A comparison of the two active treatment conditions will test whether the efficacy of CBT for PTSD following accidental injury can be enhanced with parent involvement. Importantly, the battery of questionnaires used in this study will allow assessment of whether the active treatment conditions are associated with improvements in psychological symptoms as well as health-related quality of life. Further, the design of the study will allow for an examination of improvements and maintenance of gains (for the active treatments) over a 12-month follow-up period.

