### Study Hypotheses

It is hypothesized that:

• Following treatment, compared to participants in the WLC, participants in both active treatment conditions will demonstrate significantly greater reductions in child trauma, anxiety and depressive symptoms, significantly higher ratings on a health-related quality of life measure and significantly reduced ratings of functional impairment.

• Compared to participants in the CF-CBT treatment condition, participants in the FF-CBT treatment condition will demonstrate significantly greater reductions in child trauma, anxiety and depressive symptoms, significantly higher ratings on a health-related quality of life measure, significantly reduced ratings of functional impairment, significantly greater reductions in parental anxiety, trauma and depressive symptoms and significantly increased parental perception of their own ability to support their child.

• These treatment gains (and differences) will be maintained over 6- and 12-month follow-up.

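### On the plain reading, maintenance of gains and of the family- v child-focused difference is judged on a follow-up sample enlarged by re-randomised waitlist children who were controls at post-test

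*Protocol article*

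**What the plan says.** All references are to the protocol article.

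- **Design of the Trial** gives the half crossover two purposes. The first is "to allow baseline and post-test comparisons between the two active treatment conditions and waitlist control group". The second is "increasing the sample size for the final evaluation at follow-up". To that end, "all children in the waitlist condition will be randomly allocated to one of the two active treatment conditions following their initial waiting period".
- **Stage 4 - Intervention** sets the delay: waitlist participants are "randomly assigned to one of the two active treatment conditions after 10 weeks of having been in the WLC".
- **Stage 6 - Post-intervention assessment and follow-up** plans to "recruit a total of 140 participants (approximately 45 in each condition"). It also states that "All participants will be followed up at post-intervention and 6 and 12 months following the completion of treatment", and adds a separate re-assessment of waitlist families at the end of the 10 weeks.
- **Study Hypotheses**, third hypothesis: "These treatment gains (and differences) will be maintained over 6- and 12-month follow-up".
- **Statistical Considerations** tests diagnostic status by chi-square at each assessment occasion and analyses continuous outcomes with linear mixed effects models. It does not say which children make up FF-CBT and CF-CBT at each occasion, and it names no term for immediate or deferred entry.

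**The concern.** A sample that is increased for follow-up is larger than the one used at post-test. At post-test the waitlist children are the comparator. At 6 and 12 months the same children sit inside FF-CBT or CF-CBT. If diagnosis is tested occasion by occasion on whoever belongs to each group at that time, a change between post-test and follow-up mixes two things: what happened to the children, and who was added.

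The added third differs systematically from the rest. These children go 10 weeks without treatment, and the section on early intervention itself expects PTSD rates to fall sharply in the first year and some children to recover unaided. All of them are re-allocated, so those who recover while waiting enter the treated groups already free of the diagnosis. Relapse among the immediately treated could then be masked, or an FF-CF difference that was fully held could look eroded.

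**Working it through.** **1. The plan's own figure.** Sample Size and Power Calculations gives w = 0.50, about 20% attrition and about 140 children in three groups. Alpha and power are not stated, so 140 cannot be reproduced exactly. With two-sided alpha 0.05 (assumed) and a 1-df noncentral chi-square with noncentrality N × w²:

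| Power | N in FF + CF | × 1.5 for three arms | ÷ 0.8 for attrition |
|---|---|---|---|
| 80% | 31.4 | 47.1 | 58.9 |
| 90% | 42.0 | 63.0 | 78.8 |
| 95% | 52.0 | 78.0 | 97.5 |

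So 140 is more than w = 0.50 requires.

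**2. Who is in the comparison.**
- Per arm: 140/3 = 46.7.
- FF + CF as first randomised: 2 × 46.7 = 93.3, or about 75 after 20% attrition.
- FF + CF after crossover: 140, or about 112 after attrition.
- Former waitlist share at follow-up: 46.7/140 = 33%.

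**3. When treatment starts, in weeks after admission.** Baseline is at 4-6 weeks, and the allocated condition begins one week after randomisation.
- Immediate: 4 + 1 to 6 + 1 = 5-7 weeks.
- Deferred: from 4 + 10 = 14 weeks if no one-week lag applies, to 6 + 10 + 2 = 18 weeks if the lag applies at both randomisations.

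**4. Shift in level.** Assumptions, none of them from the documents: 60% of children who have the diagnosis at the start of treatment are free of it afterwards; nobody changes after that; a share r of waitlist children recovers before deferred treatment and stays well.

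Deferred rate = r + (1 − r) × 60%. Pooled rate = (2/3) × 60% + (1/3) × deferred rate.

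| r | Deferred | Pooled at follow-up | Apparent change from 60% |
|---|---|---|---|
| 10% | 64% | 61.3% | +1.3 points |
| 30% | 72% | 64.0% | +4.0 points |
| 50% | 80% | 66.7% | +6.7 points |

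More generally, the pooled rate moves by one third of whatever gap separates deferred from immediate children. A gap of 10-20 points in either direction moves it by 3.3-6.7 points.

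**5. Dilution of the contrast.** Assume a true FF-CF difference of 20 points, fully maintained. Children who recover while waiting contribute no difference, so the deferred difference is 20 × (1 − r). The pooled difference is (2/3) × 20 + (1/3) × 20 × (1 − r) = 20 × (1 − r/3):
- r = 10%: 19.3 points (0.7 lost)
- r = 30%: 18.0 points (2.0 lost)
- r = 50%: 16.7 points (3.3 lost)

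**6. Does using the same children remove the artefact?** Under the assumptions of step 4, immediate children read 60% at post-test and 60% at follow-up. The full set, with each deferred child's own post-intervention record, reads 61.3/64.0/66.7% at both. The apparent change is zero either way.

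**7. Power if only immediate children are used.** With about 75 children at w = 0.50, power is 0.99, against more than 0.999 with 112. At w = 0.30 it is 0.74 against 0.89.

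**The case against.** The strongest reply is that the article never says deferred children are left out of FF v CF at post-test. Stage 6 gives every participant a post-intervention assessment, and the power section claims the gain from crossover without tying it to a time point. A same-children comparison is therefore possible within the text, and the exact analysis set is something an article may leave to an analysis plan. This stands in part: enlargement only at follow-up is a plain reading, not an express rule. The article does, however, state both the enlargement for follow-up and the occasion-by-occasion test, and that combination produces the problem unless it is qualified.

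A reader might infer more than the documents support:

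- *That FF v CF at follow-up is confounded by the delay.* It is not. Waitlist children are re-randomised, so deferred entry is balanced between the programmes in expectation.
- *That deferred children's change will be counted from their first baseline.* No section says so. Table 1 has a single baseline column, but it also has no column for the week-10 re-assessment, so it is not a complete waitlist schedule and cannot settle the matter.
- *That every outcome is affected alike.* The mixed model follows children over time and tolerates missing occasions, which partly mitigates the problem for continuous outcomes.

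The sizes also rest on assumed inputs. Untreated recovery of 50% in 10 weeks is an upper extreme, and holding immediate children fixed for a year sits uneasily with the decline the article expects. The dilution is small beside sampling error: with 56 per arm at 70% v 50%, the 95% interval for the difference is about ±18 points.

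**Conclusion.** The point holds in limited form. On the plain reading, the third hypothesis would be judged for diagnostic status on about 93 children at post-test and 140 at follow-up (before attrition), one third of the latter treated about 10 weeks later. The between-programme contrast at follow-up remains a randomised comparison. What can go wrong is a spurious or masked change in the level of the gains of about 1-7 points, and a dilution of the FF-CF difference of about 1-3 points. Both ranges assume 60% diagnosis-free after treatment, a 20-point difference, untreated recovery of 10-50% and no later change. The problem bears mainly on diagnosis, the outcome on which the trial was sized. It is modest, but worth correcting because the data needed are already scheduled.

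**What to change.** State the following in the analysis section:

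1. Judge the third hypothesis on the same children at post-intervention, 6 and 12 months, with each deferred child's own post-intervention assessment entered alongside the immediate children's post-test.
2. Take the week-10 re-assessment as the deferred child's pre-treatment value. This presumes that it includes the diagnostic interview, which the planned waitlist comparison on the primary outcome needs in any case.
3. Include randomisation stage (immediate v deferred) as a stratum for diagnosis, for example by Mantel-Haenszel, and as a term in the mixed model.
4. Also report the FF-CF estimate for the immediate stage alone. Stratifying makes any dilution visible but still averages over the two stages; the immediate-stage estimate is free of it.

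The cost is wording, one extra model term and a less precise immediate-only estimate. At the plan's own w = 0.50 that loss hardly matters; at w = 0.30 it would be noticeable, so the pooled, stage-adjusted estimate should be kept beside it.
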